## Abstract

**Background:**

Over 40% of Hispanic individuals have below basic health literacy levels, significantly impacting their ability to manage chronic conditions such as type 2 diabetes (T2D). Chronic disease self-management, essential for improving adherence, is often hindered by modifiable factors such as health literacy. Ambulatory care clinical (ACC) pharmacists, through comprehensive medication management (CMM), play a critical role in addressing these barriers; however, current methods for delivering CMM vary significantly, limiting effectiveness. Digital technology may offer significant potential for improving medication adherence, particularly among Hispanic individuals who use smartphones to seek health information.

**Objective:**

This study aims to revise, develop, and pilot test a culturally adapted, individually tailored digital health app designed to enhance health literacy and medication adherence among older Hispanic adults with T2D by integrating interactive educational modules into pharmacist-delivered CMM.

**Methods:**

Our team previously developed a prototype computer-delivered, culturally adapted intervention targeting health literacy and adherence among older Hispanic individuals. The proposed project involves transforming this intervention into a modernized digital health app. We will achieve 2 specific aims. The first aim is to refine and modernize previously developed content into an interactive digital health app suitable for older Hispanic adults with T2D and ACC pharmacists. A total of 20 patients and 10 ACC pharmacists will review and provide feedback on the app modules. Usability and acceptability will be measured using validated tools, including the System Usability Scale, Adjectival Ease of Use Scale, and the technology acceptance model. The second aim is to conduct a pilot test with 40 Hispanic adults (aged ≥50 years) diagnosed with T2D. Participants will be recruited from a local Federally Qualified Health Center where ACC pharmacists manage diabetes care. Patients will complete a baseline CMM session, interact with the app modules, and return for 1 or 2 CMM follow-up visits. We will assess medication adherence, hemoglobin A_1c_, and fasting glucose levels as primary outcomes.

**Results:**

The digital app has been modernized and completed for acceptability and usability testing. We will begin testing the hypothesis that the app will have above-average usability and acceptability (System Usability Scale: mean score ≥71 and Adjectival Ease of Use Scale: mean score ≥5), with an overall goal that the digital app will be acceptable (via the technology acceptance model) by ≥90% of the patient participants and ACC pharmacists. In addition, anticipated health outcomes for aim 2 include improvements in medication adherence (>80%), hemoglobin A_1c_ (≥0.75% reduction), and fasting glucose (≥25% reduction) from baseline.

**Conclusions:**

When the study is completed, it is expected that the culturally adapted digital health app will be acceptable and usable among both patients and pharmacists. Successful results will enable wider dissemination of the refined app and establish a framework adaptable to other chronic diseases, diverse languages, cultures, and health care settings.

## Introduction

### Epidemiology

The Centers for Disease Control and Prevention estimates that over 34 million people in the United States have diabetes [1]. Readmission data from the Centers for Medicare and Medicaid Services show that patients with diabetes as a comorbidity need to be targeted for high-cost and disease management [2]. Diabetes has the third-highest 30-day all-cause readmission rate among Medicaid patients, resulting in nearly 34,000 readmissions and at a cost of approximately US $471 million [3]. In addition, the prevalence of diabetes is higher among minority groups (eg, Hispanic populations). Data show that state-insured Hispanic individuals with type 2 diabetes (T2D) have poorer glycemic control and adherence to newly prescribed diabetes medications (oral or insulin) compared to non-Hispanic White populations [4]. Diabetes medication adherence rates also continue to decrease in the United States. Data suggest that patients with diabetes who had an unscheduled readmission within 90 days were more likely to be lower-income minorities on public insurance [5,6]. As a result, minority patients with T2D are more likely to have poorer health outcomes, higher risk of hospitalizations, and higher economic burden [1,2,7].

### Tailored Information and Multimedia Instruction as Interventions

The primary method of provider-patient communication about medications has traditionally been brief oral communications during often hurried medical consultations. Studies suggest that patient retention of information in this context is poor, often less than 50% [8]. The introduction of multimedia presentation of material may increase learning and retention and may be helpful for various conditions and populations [9-12]. Unfortunately, the results of using eHealth interventions for T2D have been mixed, including those focused on Hispanic populations [13-15]. Limitations that commonly plague eHealth interventions in T2D are (1) lack of cultural adaptation for minorities (such as Hispanic individuals); (2) unknown usability or operability by patients and providers; (3) educational health literacy component that is predominantly mono-directional; (4) lack of tailoring to the individual; (5) education principles of multimedia learning are not used; (6) lack of general medication information, or such information is provided by nonspecialists; (7) cost-prohibitive; and (8) lack of sufficient security of patients’ personal health information [13-15]. A recent National Institutes of Health (NIH)-funded project (R01DK112322) developed an eHealth intervention using text messaging that achieved a notable 1% reduction in hemoglobin A_1c_ (HbA_1c_) but did not show improvements in medication adherence [14,16]. While promising, the intervention encountered certain practical challenges, such as limited capacity for individual tailoring and potential security concerns associated with a cloud-based platform [16]. Accordingly, our digital health app aims to address these factors and build on the progress shown by previous interventions.

### Hispanic Smartphone and Digital Health Information Use

Similar to non-Hispanic White people, approximately 85% of Hispanic people use a smartphone daily [17]. Hispanic adults are outpacing all other groups in smartphone use growth rate. In addition, similar to other groups, Hispanic adults spend approximately 3 hours per day on a smartphone and 1 hour per day on a tablet. Hispanic individuals are more likely to use smartphones for health-related information compared to non-Hispanic White or Black populations (73% vs 58%‐67%) and more likely to view educational content (45% vs 26%‐32%) [18]. Unfortunately, misinformation across many health topics (eg, noncommunicable diseases and medical treatment) ranges between 30% and 87% [19]. In addition, the ability to interpret information could be a problem, as identified by Powell et al [20], who found that patients often misinterpret online reputable diabetes information (ie, American Diabetes Association myths). The proposed study will enable the investigators to use available technology to provide patients access to correct information, while also enabling health care providers to assess patient interpretation of the information to ensure patients understand. The use of digital apps has become common among all populations in the United States, with Hispanic individuals reporting using an average of approximately 27.9 apps and spent 41.5 hours using mobile applications per month. [21]. Therefore, Hispanic individuals may be more likely to use a digital health app to educate themselves. The digital health app proposed may improve T2D health literacy, promote patient engagement, and allow for precision counseling. Precision counseling is a personalized approach to patient education and adherence that considers social and environmental stressors, medication side effects, and health literacy to tailor interventions for each patient [22]. Similar to precision medicine, it leverages technology to optimize counseling strategies, provide more effective treatment, and potentially improve health outcomes.

### Pharmacists’ Comprehensive Medication Management (CMM) Services

Data show that health care providers may not adequately promote medication adherence due to a lack of time or by failing to use an effective communication format for the patient (eg, appropriate reading level, language) [23]. There is an increasing role for pharmacists in assisting patients with T2D. Section 10,328 of the Affordable Care Act amended section 1860D-4(c)(2)(ii) of the Act and requires prescription drug plan sponsors (Part D plans) to offer an annual medication review as part of the comprehensive medication management (CMM). CMM is a standard of care that guarantees each medication is individually assessed for appropriateness, effectiveness, and safety for the individual patient. Using CMM can improve chronic disease self-management and related outcomes. Some data suggest pharmacists can positively impact adherence and decrease HbA_1c_ (a measure of blood glucose control over time) through CMM [24]. However, other studies on the benefits of CMM are inconclusive because of limitations or failure to demonstrate efficacy in chronic disease self-management [25,26]. In these studies, researchers have used digital interventions that may not be readily comparable or optimally defined [24,25]. Limitations of these studies have included time constraints, lack of Hispanic populations, lack of integration into normal workflow, and absence of innovative digital eHealth technology (eg, individual tailoring) [27,28]. Another key limitation in these studies is their focus on adherence as an isolated problem. Given that factors affecting adherence and health outcomes are multidimensional, the content we developed and culturally adapted is multifaceted [22]. It is based not only on providing tailored content, but also on assessing modifiable factors of adherence (eg, depression). As a result, it can enable pharmacists to provide precision counseling to influence areas in which a patient shows a deficiency and be modified based on various factors of adherence.

### Synopsis of Current Culturally Adapted Intervention

We have demonstrated that health literacy is impacted by cognitive abilities, academic skills, and health knowledge [29]. Based on these results, we developed and culturally adapted a health intervention for older Hispanic adults with T2D using Adobe Captivate [22]. This intervention suggests favorable results regarding usability among patients and pharmacists providing CMM. Overall, there are 3 modules that provide information, verify understanding of content with queries, and allow the patient to tailor their education (eg, knowledge about medications they take). There are also queries on other factors impacting adherence (eg, depression and cost) that will assist the provider in addressing or referring the patient to other services (eg, mental health support). This differs from other digital technologies that do not incorporate all these measures. For example, some tools take an innovative approach by using issue cards to explain medication classes but do not appear to verify knowledge gained or explain how the tool can be linked to prescribers managing their diabetes in a simple format [30]. Another novel digital app focused on Spanish speakers sends 2‐3 motivational texts per day, but also does not appear to collect knowledge gained or provide specific information regarding their medications [14,31].

### Aims and Hypotheses

There are 2 aims in the proposed study. Aim 1 consists of refining and modernizing developed diabetes content from our previous study [22], developing the Patient and Provider apps, and testing the usability and acceptability by patients and pharmacists. The Aim 1 hypothesis is that the digital apps (ie, Patient and Provider apps) will have above-average usability and acceptability (System Usability Scale [SUS] mean score ≥71 and Adjectival Ease of Use Scale [AEOUS] mean score ≥5) with an overall goal that the digital apps will be acceptable (Davis’ technology acceptance model [TAM] ≥90%) to the participant patients and pharmacists.

The goal for Aim 2 is to pilot test the digital health apps to assess adherence and health outcomes in 40 Hispanic patients with T2D. The Aim 2 hypothesis is that the digital health apps will improve adherence (>80% average adherence for the individual), HbA_1c_ (≥0.75% reduction), and fasting glucose (≥25% reduction) from baseline.

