### Phase III

The third phase will test health outcomes: medication adherence, HbA_1c_, and fasting blood glucose. During this phase, the pharmacist will use the digital health app with 40 adult Hispanic patients with T2D who meet the inclusion requirements (stated under the ”Recruitment” section). The study will take place at the Athens Neighborhood Health Center. If by 6 months, we have not recruited at least 25 patients, we will pursue another local federally qualified health center. After consent, patients will be instructed on downloading the digital health app, completing the modules within the first 2 weeks, and generating the QR code. Their preference for either submitting the QR code via email or bringing it to their next appointment will be confirmed. Medication adherence will be measured using scales previously used by the investigators (the Gonzalez-Lu questionnaire and the visual analog scale) [49,50]. The Gonzalez-Lu questionnaire and visual analog scale are being used due to their ease of use and strong reliability and correlation to electronic measurements of medication adherence [51-53]. Baseline HbA_1c_ and blood glucose levels (fasting) will be measured via labs conducted as standard medical practice. A follow-up visit will occur 3‐4 months later. Depending on patients’ responses, an additional visit 3‐4 months later may be needed. The app would immediately assist a patient who is nonadherent due to not knowing how to take a medication (eg, the app would explain that taking metformin with food optimizes effectiveness and lowers side effects). However, a patient may be nonadherent due to the inability to pay for a particular medication; this would be captured by the app but not addressed immediately because they chose to provide their QR code at the follow-up appointment and not when the issue arose. In such a scenario, the patient would have a follow-up visit an additional 3‐4 months after appropriate changes are made (eg, selecting another medication). In summary, Phase III will test our Aim 2 hypothesis that the app will improve medication adherence (>80% average adherence for the individual), HbA_1c_ (≥0.75% reduction), and fasting glucose (≥25% reduction) from baseline. These reductions are reasonable target endpoints based on the literature [54-56].

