The primary endpoint of Aim 2 is to improve adherence and health outcomes. We completed power analyses for this aim using a mixed-effects simulation routine in Power Analysis Sample Size (PASS 16; NCSS, LLC) software, and drawing effect size estimates from the literature on the impact of pharmacist counseling on diabetes control [59,60]. This analysis shows our planned sample size of 40 will provide a power of 0.85 to detect a significant change from baseline in outcome measures. Outcome measures include improvements in adherence and a reduction in HbA_1c_ and fasting glucose. We will evaluate differences before and after the intervention (eg, 3‐8 months later) using repeated-measures mixed-effects models, enabling us to evaluate not only the significance of change but also the impact of key covariates (age, gender, and health literacy) and effect size for use in planning a larger trial.

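### The Aim 2 hypothesis is stated as numerical targets, but the stated power and significance test concern only whether there is any change from baseline

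*Protocol article*

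**What the plan says.** Under Aims and Hypotheses, the protocol article states that the digital apps will "improve adherence (>80% average adherence for the individual), HbA_1c_ (≥0.75% reduction), and fasting glucose (≥25% reduction) from baseline". The Phase III section repeats the three figures and commits to testing them: "Phase III will test our Aim 2 hypothesis that the app will improve medication adherence". It adds: "These reductions are reasonable target endpoints based on the literature". The Results section gives the same figures as what the investigators expect.

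The Aim 2 paragraph under Procedures describes the test. On power it says that "our planned sample size of 40 will provide a power of 0.85 to detect a significant change from baseline in outcome measures", with the inputs described only as "drawing effect size estimates from the literature on the impact of pharmacist counseling on diabetes control". The analysis is by repeated-measures mixed-effects models, "enabling us to evaluate not only the significance of change but also the impact of key covariates". The same sentence adds an effect size, to inform the design of a later, larger trial. None of the three target values appears in this paragraph, and no section says how they will be judged.

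**The concern.** The hypothesis and its test ask different questions. The hypothesis asks whether HbA1c fell by at least 0.75, whether fasting glucose fell by at least a quarter, and whether the individual patient's adherence exceeds 80%. The test asks whether the mean of each outcome moved at all. The article does not spell out a null value of zero, but that is the ordinary meaning of a significant change from baseline.

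Two things follow. First, a real but small mean change can be significant while falling short of its target. If significance is then taken as support for the hypothesis as worded, the pilot will seem to have shown more than it did. This matters because the result is meant to lead to a larger controlled trial (Evaluation Outcomes) and the pilot has no control group (Limitations). Second, the adherence target is a level reached by a patient, not a mean change. Everyone enters below 80% adherence (Recruitment), so the mean could rise significantly with few patients, or none, crossing 80%. The planned test would not reveal this.

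**Working it through.** **Inputs from the article.** N = 40; power 0.85 for a significant change from baseline (Procedures, Aim 2); HbA1c target 0.75, read as percentage points; single-arm, before-and-after design.

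**Inputs not given, so assumed.** Two-sided 5% significance, no dropout, and an SD of the individual HbA1c change of 1.0, 1.5 or 2.0 points. The comparison is simplified to a paired t-test on change with 39 degrees of freedom.

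**Step 1: the article's own figure.** The 0.85 cannot be reproduced, because effect size, SD, within-patient correlation, significance level and sidedness are not stated. It can only be solved backwards. With 40 patients, 85% power corresponds to a standardised mean change of 0.486 (noncentral t, two-sided 5%). The normal approximation gives (1.960 + 1.036)/√40 = 0.474. With a one-sided 5% test the values are 0.432 and 0.424. If the powered effect had been 0.75 HbA1c points, the implied SD of change would be 0.75/0.486 = 1.54 points. The article does not say that this was the powered effect.

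**Step 2: the smallest mean HbA1c drop that is significant.** This is t(0.975, 39) × SD/√40 = 2.023 × SD/6.325.

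- SD 1.0: 2.023 × 0.158 = 0.32
- SD 1.5: 2.023 × 0.237 = 0.48
- SD 2.0: 2.023 × 0.316 = 0.64

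All three are below 0.75. Observed drops between the cut-off and 0.75 are significant and miss the target.

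**Step 3: how often significance arises when the true mean change misses the target.** The table gives the probability of rejecting no change.

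| SD of change | True drop 0.40 | True drop 0.75 |
|---|---|---|
| 1.0 | 0.69 | 0.996 |
| 1.5 | 0.38 | 0.87 |
| 2.0 | 0.24 | 0.64 |

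A true mean drop of 0.40, about half the target, is declared significant between roughly a quarter and two thirds of the time.

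**Step 4: what the estimate can add.** The 95% CI half-width for the mean change has the same formula as the cut-off in step 2, so it is about 0.32, 0.48 or 0.64 points. Set beside 0.75, the interval answers the question that the p-value leaves open.

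**Step 5: adherence and glucose.** No arithmetic is possible without data. The adherence target calls for a count of patients above 80%, which is a proportion, and a test of mean change does not estimate one. The glucose target is a relative change. The article does not state the model's scale, so it cannot be said that the model fails to estimate this quantity, only that the text does not tie the model to it.

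**The case against.** The strongest defence is that the figures are anticipated sizes, not null values. The verb is improve, the numbers stand in parentheses, the Abstract calls them anticipated outcomes, and Phase III calls them target endpoints. In an admittedly small, uncontrolled pilot, a test of improvement with descriptive benchmarks beside it is quite normal. This defence has weight, and the fix adopts that reading. It does not remove the problem, because Phase III says that the hypothesis containing the figures will be tested, and nothing in the article marks them as descriptive.

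A reader might go further and infer that the planned model cannot confirm or refute the hypothesis. The article does not support that. It is true of a p-value against no change, but the model also yields an effect estimate, which the article plans to obtain. Its interval could be compared with 0.75 and, on a relative scale, with 25%. The article assigns that estimate to planning the next trial, so its use in judging the targets has to be stated.

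A reader might also infer that the power of 0.85 is wrong. That is not shown. Its inputs are not given, and it may be correct for the question it addresses, which is improvement.

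**Conclusion.** The point holds as a mismatch between a stated hypothesis and its stated test. Both are in the article, so this is not detail left to an unseen analysis plan. Significance against no change does not establish that any target was met, and the individual-level adherence target is not addressed by a test of mean change.

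For HbA1c, the gap between a significant result and a target-sized one runs from a cut-off of about 0.32 to 0.64 points up to 0.75. That range rests on the assumed SDs of 1.0 to 2.0, two-sided 5% and no dropout. The mismatch itself needs none of these assumptions. No size can be given for glucose or adherence. The correction is worth making before Phase III starts. It does not call the design or the sample size into question.

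**What to change.** In Aims and Hypotheses, Phase III and the Aim 2 analysis paragraph:

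- Word the tested hypothesis as mean improvement from baseline in each outcome, and attach the 0.85 to that alone.
- Label the three targets as descriptive pilot benchmarks.
- Report against them the mean HbA1c change in percentage points with a 95% CI, the percent change in fasting glucose with a 95% CI (for example back-transformed from a log-scale model), and the proportion of patients above 80% adherence with an exact CI.
- State that no target will be called met on the strength of significance against no change.

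A formal rule requiring the confidence bound to lie beyond the target is not recommended for this pilot. For HbA1c it would succeed only 2.5% of the time if the true drop were exactly 0.75. Under the same assumptions, an 85% chance of success would need a true drop of about 1.24, 1.48 or 1.72 points at SDs of 1.0, 1.5 or 2.0.

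The cost is a few sentences and, for glucose, possibly a transformation. No extra patients or visits are needed. The downside is a slightly weaker claim: outcomes improved, with the targets described and not confirmed.
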